**Table 3. Tool for causality assessment of serious adverse events**

| Relationship                                                                            | Description                                                                                                               |
|-----------------------------------------------------------------------------------------|---------------------------------------------------------------------------------------------------------------------------|
| Definitely                                                                              | Temporal relationship
Improvement after dechallenge*
Recurrence after rechallenge
(or other proof of drug cause) |
| Probably                                                                                | Temporal relationship
Improvement after dechallenge
No other cause evident                                          |
| Possibly                                                                                | Temporal relationship
Other cause possible                                                                             |
| Unlikely                                                                                | Any assessable reaction that does not fulfil the above conditions                                                         |
| Not related                                                                             | Causal relationship can be ruled out                                                                                      |
| *Improvement after dechallenge only taken into consideration, if applicable to reaction |                                                                                                                           |

In addition, a severity assessment of the event (mild, moderate or severe) will be performed. Mild means the complication is tolerable, moderate means it interferes with daily activities and severe means it renders daily activities impossible.

Serious adverse event and suspected adverse reaction (patient reported) will be documented in an Serious adverse event log and evaluated by the study team every 3 months.

In case of serious suspected adverse reactions users call the study office and appropriate measures will be taken within 48 hours.

---

## 10 STUDY PROCEDURES

### 10.1 Pre-screening and pre-study screening log

The pre-screening of potential study participants will be carried out by a web page. In case of eligibility an app access code is provided. Every participant who shows interest in the study on the webpage is anonymously counted in a digital pre-study screening log. Furthermore, every participant who fulfills the prescreening criteria and receives a code to complete a 28 days baseline in the M-sense control app is anonymously counted in a digital pre-study screening log. The anonymous data will be used to describe the participant selection in a flow chart.

### 10.2 Baseline and informed consent

With the access code the control app can be used for a 28 days baseline assessment as recommended for migraine studies. The participants will receive privacy information within the app and their electronic consent will be obtained.

The data will be used at the end of the baseline phase to assess the eligibility for the study. Close to the end of the baseline phase the migraine diagnosis will be confirmed in a video consultation by a physician, the main study eligibility will be checked and the informed consent will be obtained. The informed consent includes general information about the study, inclusion and exclusion criteria, the course of the study, the study tasks, data gathering and data use, the risks, privacy, time commitment, and the withdrawal procedures. Eligible patients who provided informed consent will receive a study code from the physician. After they completed the baseline phase the control app checks the in-app eligibility criteria (migraine  $\geq 3$ , filling in of the diary, no medication overuse). All other eligibility criteria will be checked by the physician. Participants who do not fulfill eligibility criteria will be offboarded by the app and their data will be deleted.

### 10.3 Randomization

Eligible participants will then be asked by the app to enter the study code received from the physician and will be randomized within the app. They participate in the DiGA study for 12 weeks according to their treatment allocation. After the end of the DiGA study the intervention group keeps the M-sense Migräne app and the control will also receive access to all the features of the M-sense Migräne app. Both groups will participate in a 12-weeks in a follow-up study.

## 10.4 Procedures in case of pregnancy

Although pregnant women will not be included into the study because hormonally change can influence the headache and migraine days, patients who become pregnant during the study period will not be excluded. This decision was made because we use an intention-to-treat population for the analysis and the interventions within the app are not known to have risks for pregnant women.

## 10.5 Discontinuation of the study

The study will be discontinued if less than 10% of the anticipated number of participants are recruited within the recruitment time.

# 11 STATISTICAL METHODS AND DETERMINATION OF SAMPLE SIZE

## 11.1 Sample size calculations

The following assumptions as basis for the sample size estimation are based on a pilot project: reduction of migraine days in the intervention group 1.69 migraine days, and in the control group 0.42 migraine days. This resulted in a group difference of 1.27 migraine days in week 9-12 between both groups with a pooled standard deviation of 4.20. Applying a 2-sided T-test for independent groups with a power of 80% and an alpha of 5%, a total of 173 participants will be needed per group (346 participants in total for both arms). Because the primary analyses will follow the intention-to-treat (ITT) principle, all randomized patients will be included and missing data will be imputed, additional patients to compensate for dropouts have not been taken into account. The sample size was calculated with the software PASS 2008 (Version 08.0.16, Release 27.01.2011; Hintze, J. (2008), NCSS, LLC, Kaysville, Utah). The rationale for the assumptions has been described in the SAP (Version 2.1).

## 11.2 Analysis plan

A detailed statistical analysis plan (SAP) has been written (version 1.0 November 22, 2020) and accompanies this evaluation concept. For details please refer to the SAP.

## 11.3 Primary comparison and hypotheses

The primary analysis is a comparison of the group receiving the M-sense Migräne app with the group receiving the control app for the primary outcome (migraine days in weeks 9-12).

The following hypotheses will be tested:

$H_0$ : the migraine days in week 9-12 are **not** different between the intervention and the control groups

In case  $H_0$  can't be confirmed  $H_A$  will be adopted

$H_A$ : the migraine days in week 9-12 are different between the intervention and the control groups

## 11.4 Analysis populations

Based on the ITT principle, participants will be analysed in the which they were randomized, and we will include all patients in the analyses. This and other populations have been described in the SAP.

## 11.5 Participants demographics and baseline characteristics

All available baseline data will be analysed descriptively per group and in total. Results will be reported as means with standard deviations or as frequencies and percentages.

## 11.6 Primary outcome definition

The primary outcome are the **migraine days per month** (defined as 28 days) after 12 weeks (week 9 to 12). Migraine days will be based on the information in the headache diary. Headache attacks will be classified according to ICHD-3 (criteria B to D) by a physician blinded for the patient's group allocation (see SAP 2.1 for further description). A migraine day is defined as a calendar day on which a single or multiple migraine attacks have been reported. The number of migraine days per month is obtained by adding up the number of migraine days within four consecutive weeks (28 days).

## 11.7 Analysis of the primary outcome

The analysis for the primary endpoint (migraine days week 9-12) will be conducted using an analysis of covariance (ANCOVA) with the treatment group (intervention/control) as fixed factor and baseline migraine days and type of migraine (episodic/ chronic as stratification variable during randomization) as covariates. From this model, estimated means and 95% confidence intervals will be obtained. Missing data will be imputed by using adequate multivariate imputation methods. In case of relevant differences in baseline variables between the treatment groups, the analysis of the primary outcome will be repeated with the additional adjustment for these variables.

## 11.8 Secondary outcomes

Secondary outcomes will be analysed similarly to the primary analysis, i.e. ANCOVA, or logistic or Poisson regression (depending on the scale and distribution of the data), adjusted for sex and the respective baseline value (when available). Detailed description of all analyses will be given in the SAP.

All analyses on secondary outcomes will be considered explorative.

## 11.9 Further analyses

As supportive analysis models for repeated measures will be fitted to compare the groups with respect to changes in the primary outcome over time. Further details will be described in the SAP.

## 11.10 Analyses of safety outcomes

All safety variables will be tabulated (in total and per treatment group). Reported are number of participants with suspected adverse reactions, serious suspected adverse reactions, and adverse events, number of participants who withdraw from the study due to suspected adverse reactions. Categorical variables are reported using frequency and percentage, continuous variables are reported by giving descriptive measures (mean, standard deviation/standard error, quartiles, and range). The evaluation of safety endpoints is performed with the safety population.

## 11.11 Interim analyses

No interim analyses are planned.

# 12 QUALITY CONTROL AND QUALITY ASSURANCE

## 12.1 Data Management

The trial will be conducted according to the Standard Operating Procedures (SOPs) and the quality management protocols of the Institute for Social Medicine, Epidemiology, and Health Economics and of Newsenselab. Newsenselab is responsible for the central storage of the collected data and will transfer the data adequately encrypted and via a safe transfer method as a csv-file to the study investigators. The data are coded with the EMMA-ID (pseudonymization) rather than with clear names, so that it is not possible to assign them directly to the study participants. The access to the linked person identifying data (such as name and contact information) is restricted (physician who obtains informed consent and defined personal of the study office at the Charité). Study investigators will work with aggregated pseudonymized data and will only publish data in anonymized form. Data received from Newsenselab will be checked for plausibility, correctness, and completeness. After a blind review data will transposed to a SPSS file or similar format for statistical analysis.

## 12.2 Data monitoring

M-sense Migräne's data validity is established as a CE marked medical device and reviewed regularly as part of its quality management system. An audit trail log covering the data trail from each participant's

data entry to the export will be reviewed by the study investigators. Further procedures to test data validity will be established by the investigators.

## 13 ETHICS AND REGULATIONS

This study will follow the standards of the Helsinki Declaration (1996 version, Somerset West) and will be based on ICH-GCP guidelines. The study is approved by the responsible ethics committee (Charité – Universitätsmedizin Berlin; EA1/343/20). The study is also subject to review by the data protection officer of the Charité – Universitätsmedizin Berlin. The study participants have the right to obtain information about the data collected about them at any time. Participation in the study will be voluntary and will only take place after written consent has been given following detailed explanation of the study contents and objectives. Participation in the study can be terminated by the patient at any time without any disadvantages for the patient.

The study will be conducted according to § 23 b MPG (Medizinproduktegesetz) – exemption of clinical investigation. Although randomized the study follows a routine care setting usage of the app. There are no invasive study procedures and most of the documentation for the study has been already implemented as a routine care measure of the app (e.g. diary). The physician visit for the diagnosis reflects a typical diagnostic case taking of migraine patients. The M-sense Migräne app will be used only within the intended purpose.

EU General Data Protection Regulation (GDPR) as well as the Berlin and the Federal Data Protection Acts are applied. Both Newsenselab GmbH and the Institute for Social Medicine, Epidemiology and Health Economics have established quality management systems. A privacy policy for the study and the app will be available. We will collect only data which is necessary for the study. The access to the linked person identifying data (such as name and contact information) is restricted (physician who obtains informed consent and defined personal of the study office at the Charité). Study data is stored encrypted on Newsenselab's servers during the study. Any data transfer between the app and the servers is state-of-the-art encrypted. A detailed data protection concept for the study will be developed based on the SMARTGEM study funded by the Innovation Fund.

### 13.1 Insurance

No special insurance is purchased for the patients for this study. The Charité employees involved in the study are insured by the public liability insurance of Charité – Universitätsmedizin Berlin against liability claims that could result from their culpable behavior.

## 13.2 Study registration

This trial will be registered after ethics and BfArM approval in the German Register for Clinical Trials (DRKS; [https://www.drks.de/drks\\_web/](https://www.drks.de/drks_web/)).

## 14 PUBLICATION

Results of the study will be made publicly available within 12 months after end of the study, if necessary as pre-print. We will submit the results of the study to peer-reviewed international journals. The chances of a manuscript being accepted by a medium to high ranked journal are considerable, presuming that the results of the study are conclusive.

## 15 STUDY SCHEDULE

The study will follow the following schedule:

- Baseline First-Participant-In: January 1, 2021
- Study First-Participant-In: January 29, 2021
- Baseline Last-Participant-Out: June 30, 2021
- Study Last-Participant-Out: Sep 30, 2021
- Data Analysis and report to BfArM: Dec 15, 2021

## SAP Revision History

| Previous Version | Updated Version | Sections changed                                                            | Description and reason for change                                                                                                                          | Date of change |
|------------------|-----------------|-----------------------------------------------------------------------------|------------------------------------------------------------------------------------------------------------------------------------------------------------|----------------|
|                  | 0.0             |                                                                             | Creation of document                                                                                                                                       | 10.11.2020     |
| 0.0              | 1.0             |                                                                             | First final version                                                                                                                                        | 22.11.2020     |
| 1.0              | 2.0             | Sections 1, 2, 3, 5, 6.1, 6.2, 7, 8, 10.4.1-10.4.3, 10.5.1, 10.5.3, Table 2 | Change of primary outcome as requested by the regulatory authority (BfArM), specification of handling of missing data, adaption of sample size calculation | 05.12.2020     |
| 2.0              | 2.1             | Sections 3, 6.1                                                             | Change of attack classification                                                                                                                            | 09.12.2020     |

Authors: [name] and [name], [name], [name]

Institute for Complementary and Integrative Medicine, University Hospital Zurich and University of Zurich

Institute for Social Medicine, Epidemiology and Health Economics, Charité – Universitätsmedizin Berlin

## 1 INTRODUCTION

This is the Statistical Analysis Plan (SAP) for the digital health application (DiGA) study: ‘Effectiveness of the M-sense Migräne app – a randomized controlled study - EMMA Study’, that substitutes the evaluation concept (version 2.1). The study has been approved by the ethics committee of the Charité – Universitätsmedizin Berlin (EA1/343/20). This SAP describes only the analyses for the 12-weeks DiGA study period. An additional SAP for the 24-weeks follow-up study that is outside DiGA study will be developed in the first half of 2021.

## 2 AIM OF THE TRIAL

The aim is to evaluate the effectiveness of the M-sense Migräne app in reducing migraine days in patients with episodic migraine and chronic migraine compared to patients in a waiting list control group who have no access to the app intervention features.

## 3 STUDY DESIGN

This is a two-armed, open-label, parallel-group, randomized study. Patients will be randomly allocated to one of two groups (intervention or control as a waiting list) in a 1:1 ratio (stratified for episodic and chronic migraine) to gain access either to the intervention (M-sense Migräne app) or an app version with only data input features (control app). For motivational reasons the control group participants will automatically gain access to the M-sense Migräne app after 12 weeks. These additional data and the 24-weeks follow-up in the intervention group that uses M-sense Migräne from the beginning will not be part of the DiGA study.

Methodological considerations: When planning the trial and the data analyses we were aware that the patients cannot be blinded to the group they are allocated to, which might introduce bias. However, because of the type of intervention blinding is not possible and open-label trials are common in behavioral interventions. Nevertheless, the physician classifying the headache attacks and the statistician performing the analysis will be blinded for the group allocation of the patients.

Because the number of migraine days is higher in patients with chronic migraine than in patients with episodic migraine, we use the specification of diagnosis as stratification variable during the randomization.

To reduce missing data for the primary outcome, patients are reminded within the app to complete the daily headache question and document their headaches thoroughly. Furthermore, we motivate

those patients who are non-adherent and stop the intervention to at least document their headaches within the app. Based on this we can distinguish in the group using M-sense Migräne between study dropouts and intervention dropouts (see 10.4.).

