|                                   | health-related quality of life, safety, adherence, migraine-specific health literacy, and headache management self-efficacy of M-sense users.                                                                                                                                                                                                                                                                                                                                                                                                                                                                                                                                                                                                                                                               |
| Study design               | This is a two-armed, open-label, parallel-group, randomized, controlled study. Patients will be randomly allocated to one of the two groups in a 1:1 ratio to gain access either to the full M-sense Migräne app or the Control study app with only data input features. For motivational reasons the control group participants will gain access to the full M-sense Migräne app after 12 weeks. This additional data and the 24-weeks follow-up in the intervention group will not be part of the DiGA-study.                                                                                                                                                                                                                                                                                             |
| Interventions and controls | Intervention group: M-sense Migräne app for 12 weeks.
Control group: Control study app that only includes data input features (as a diary visible for one week without attack classification) and questionnaires. There will be no app interventions and no data will be feedbacked to the patients.                                                                                                                                                                                                                                                                                                                                                                                                                                                                                       |

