## 4 INVESTIGATION AND PROCEDURES

### 4.1 Overall study design

This is a two-armed, open-label, parallel-group, randomized, controlled trial. Potential study participants will be invited to participate in a 28-days baseline phase in which data on headache days and migraine attacks will be collected. This data will be used for the eligibility check. Furthermore, a physician (via video consultation) will inform about the study, validate the patient-reported migraine diagnoses and obtain the informed consent from study participants. After final informed consent and verification of the patient's eligibility for the study in the video consultation, patients will be randomly allocated to one of the two groups in a 1:1 ratio to gain access either to the full M-sense Migräne app or the control study app with only data input features (only as a diary visible for one week without attack classification with daily headache question and questionnaires, no app interventions and no feedback on data or behavior). The primary outcome will be the migraine days per month (defined as 28 days in weeks 9 to 12).

The DiGA-study will be completed after 12 weeks follow-up per study participant.

Additional data will be collected afterwards. Then both groups receive the full M-sense Migräne app and use the intervention for 12 weeks (see Figure 1). This will allow to gather data over 24 weeks in the intervention group and increase the motivation in the control group to participate in the study and to provide data over 12 weeks without access to the intervention.

[figure not shown]

Figure 1. Study flow and design of RCT

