## 4 INTERVENTION AND CONTROL

The intervention group receives the M-sense Migräne app in the DiGA study for 12 weeks. The app includes the following features: a) Headache reporting and attack classification diary; b) Medication intake diary; c) Trigger factors diary; d) Analysis function and physician report; e) Personalized education on disease- and trigger management; f) Relaxation therapy; g) Training module; h) Acute pain therapy, and i) Behavioral Change Techniques.

The control group will use within the 12 weeks an app (“control app”) that only includes data input features (headache reporting and diary and medication intake diary) and questionnaires. The headache diary will not show any attack classification, analysis or aggregated reports on the documented data to the patient. The headache diary is limited to the last seven days, which means that patients cannot enter or edit headache attacks or medication intakes that date back seven days or longer. The control app does not contain any of the other abovementioned app interventions.

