- Headache attributed burden such as disability and headache attributed lost time is measured with the 5-item Headache-Attributed Lost Time indices (HALT-30^10, official German translated Version) over the last 30 days after 12 weeks. The HALT-30 was developed as part of "The Global Campaign against Headache" with support from the World Health Organization. The HALT items are fully based on the five MIDAS items with slightly changed wording for more clarity and a shorter retrospective reporting period (30 instead of 90 days). Because of this, the HALT-30 can be viewed as an improvement of the MIDAS and the indices show no changes to the structure and scoring of the well-validated MIDAS.
- Migraine-specific health literacy after 12 weeks (3 items, own development) with the items prophylaxis literacy, disease literacy, trigger literacy on a 4 point Likert-type scale from 1="sehr gut" to 4="sehr schlecht".

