## 10 STATISTICAL ANALYSES

### 10.1 TIMING OF ANALYSES

The duration of the DiGA study is planned to be 16 weeks per patient (4 weeks baseline plus 12 weeks of intervention). About 14 weeks after the last patient has been randomized to the study groups, the clean file will be prepared to start the analysis of this DiGA study.

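### Controls get the full app automatically at 12 weeks, when their only follow-up questionnaires fall due, and no rule puts the questionnaires first

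*Combined protocol and SAP*

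**What the plan says.** **The switch.** SAP section 3: "For motivational reasons the control group participants will automatically gain access to the M-sense Migräne app after 12 weeks". The protocol synopsis has the same rule without the word for automatic: "For motivational reasons the control group participants will gain access to the full M-sense Migräne app after 12 weeks". Protocol 10.3 places access after the DiGA study: "After the end of the DiGA study the intervention group keeps the M-sense Migräne app and the control will also receive access". Protocol 4.1 defines that end by elapsed time: "The DiGA-study will be completed after 12 weeks follow-up per study participant". None of these makes access depend on a completed assessment.

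**The forms.** Table 1 in both documents schedules HIT-6, HMSE-G-SF, HALT-30 and health literacy once before randomization and once at week 12 within the DiGA study. A safety form is due at week 12 as well. SAP 6.2 words the literacy item as "Migraine-specific health literacy after 12 weeks (3 items, own development"; SAP Table 2 gives week 12 as the measurement time. No response window is stated.

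**Data closure.** SAP 10.1: "About 14 weeks after the last patient has been randomized to the study groups, the clean file will be prepared".

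**The diary.** For the control app, SAP section 4 says "patients cannot enter or edit headache attacks or medication intakes that date back seven days or longer". Neither document says whether that limit carries over once a control has the full app.

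**Status of the outcomes.** SAP 9.1 makes only the primary analysis confirmatory. SAP 10.5.4 and protocol 11.8 call the secondary outcomes explorative.

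**The concern.** The trial compares the app with controls who lack its intervention features (SAP section 2). A week-12 form that a control completes after the unlock no longer measures that state. Each of the four questionnaires has one follow-up value in the DiGA study, so there is no earlier unexposed value to fall back on.

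Health literacy is the most exposed. It has no stated recall period, and protocol 7.1 describes 20 education lessons in the full app. HIT-6 and HALT-30 are exposed only through the part of their recall period that falls after the unlock. HMSE-G-SF is described inconsistently: the synopsis treats it as a current state, while protocol 6.3 and SAP 6.2 give the last 4 weeks.

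The exposure is in one arm only and would generally hide a benefit. In protocol Table 2, self-efficacy and health literacy are the only outcomes mapped to patient-relevant improvement of structure and processes. A diluted comparison there weakens the only planned evidence for that category.

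**Working it through.** **1. Order of events.** The unlock is triggered by elapsed time (SAP 3). The end of the DiGA study is also set by elapsed time (protocol 4.1). The forms are due at week 12 or after 12 weeks (synopsis, SAP 6.2, SAP Table 2). A form submitted on time precedes or coincides with the unlock; a form submitted late follows it. No provision rejects the late form or assigns it to the follow-up study.

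**2. Room for late forms.** The clean file is prepared about 14 weeks after the last randomization: 14 - 12 = about 2 weeks after the last participant's week 12, and longer for everyone randomized earlier. SAP 10.1 does not say that late forms are accepted throughout that time, but no earlier cut-off is given.

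**3. Recall overlap.** Share of the recall period spent with the full app = days after unlock / recall length.

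| Days after unlock | 28-day recall (HIT-6) | 30-day recall (HALT-30) |
|---|---|---|
| 7 | 7/28 = 25% | 7/30 = 23% |
| 14 | 14/28 = 50% | 14/30 = 47% |

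These are shares of exposure, not estimates of bias.

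**4. Dilution.** Let f be the share of controls who answer after the unlock and e the share of the app's effect D they have gained by then. The control mean moves by f × e × D toward the app arm, so the observed difference is D × (1 - f × e). The documents give neither f nor e; both ranges are assumptions. Shrinkage f × e:

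| f | e = 25% | e = 50% | e = 100% |
|---|---|---|---|
| 5% | 1.25% | 2.5% | 5% |
| 10% | 2.5% | 5% | 10% |
| 30% | 7.5% | 15% | 30% |

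**5. Primary endpoint.** The plan's sample size reproduces: for a difference of 1.27, SD 4.20 and two-sided alpha 0.05, t-test power is 0.7985 at 172 and 0.8008 at 173 per group, hence 173. The primary window (weeks 9-12, days 57-84) ends before the unlock. If the seven-day limit carried over, at most days 79-84 could be entered or edited after it: 6/28 = 21%. As a deliberately extreme bound, suppose late entry passed the full effect on to those six days in a share f of controls, giving a difference of 1.27 × (1 - 0.214 × f):

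| f | Difference | t-test power |
|---|---|---|
| 10% | 1.24 | 78% |
| 25% | 1.20 | 76% |
| 50% | 1.13 | 71% |
| 100% | 1.00 | 60% |

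The lower rows are not realistic. The six days were lived without the intervention, so only recall or editing could change, and six days are open only on day 85, one fewer on each day after.

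**The case against.** The strongest reply is that the intended order is already stated. Protocol 10.3 gives access after the DiGA study ends, and SAP 3 keeps the additional data out of the DiGA study. SAP section 4 also has controls using the control app, which contains the questionnaires, within the 12 weeks, so the forms may be meant to come first. This stands as evidence of intent, and it rules out saying that the plan schedules the forms after the switch. It does not close the gap. The order rests on elapsed time alone, and the exclusion of additional data does not say which study a late week-12 form belongs to.

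The stakes are also limited. The outcomes are exploratory, and bias toward no difference cannot create a false claim of benefit. That stands.

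A reader might infer three stronger points, which the documents do not support:
- **The primary diary data are contaminated.** The seven-day limit is stated for the control app only, the days concerned precede the unlock, and a blinded physician classifies attacks from the raw diary. Protocol 12 adds an audit-trail review and a blind data review.
- **Self-efficacy is affected at once.** That depends on the synopsis wording; both outcome sections give a 4-week recall.
- **The dilution has a known size.** Any figure depends on assumed f and e.

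**Conclusion.** The gap is real and confined to the week-12 questionnaires. The unlock is automatic and time-based, and nothing keeps a control form completed after it out of the DiGA analysis. Such forms would dilute exploratory comparisons toward no difference: most clearly health literacy, partly HIT-6 and HALT-30 through recall, and HMSE-G-SF to a degree that depends on which of its two descriptions applies. The size cannot be determined from the documents; about 1-30% is what the assumed ranges produce. The confirmatory primary result is little affected, and the sample size stays at 173 per group. This is a worthwhile, inexpensive improvement and not a threat to the main conclusion.

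**What to change.** **Protocol 10.3 and SAP 3.** Replace the automatic unlock. The full app opens to a control participant when the week-12 questionnaires and safety form are submitted, or at a fixed closing date if they are not, for example one week after day 84 (day 91).

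**SAP 6.2 and 10.4.3.** Apply the same closing date in both arms. Treat week-12 questionnaires submitted after it as missing and impute them under the rule already in 10.4.3. Every counted control form then precedes that participant's access. Record the unlock and submission times so that this can be verified.

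**Diary.** Do not freeze weeks 9-12 at the unlock. The app arm has no unlock, so a freeze of that kind would bind controls only and create unequal recording on the primary endpoint. If diary entry for weeks 9-12 is locked at all, use the same cut-off relative to randomization in both arms.

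**Cost.** One rule in the app configuration and a few sentences in the two documents. Some controls wait up to about a week longer for the full app, and a few late forms become missing. Because access is offered as an incentive, tying it to submission may also improve completeness.
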